### Randomization procedures

Random number will be generated by a computerized random-number generator at statistics research office, Fourth Military Medical University. A clinical research associate will make opaque blinded envelopes (with consecutive numbers) and deliver them to each participating center. Random allocation will be performed within 12 hour after a patient enrolled. The block size and treatment-assignment table will not be available to the researchers until the end of the trial.

### Inclusion criteria

All patients presenting to the study center are eligible for inclusion in the study if they fulfill the following requirements:

1. Age: 18 to 75 years

2. The degree of ICA/MCA stenosis is greater or equal to 50% confirmed by DSA

3. Before HES treatment, CTP imaging shows that TTP in MCA territory is extended (≥15%) in comparison with that in corresponding area of contralateral hemisphere

4. If cerebral infarction appears,

① Time of stroke onset: 72 hours-3 weeks

② Magnetic resonance imaging (MRI) + diffusion weighted imaging (DWI) shows ischemic stroke due to unilateral ICA or MCA stenosis infarcts

③ NIH stroke scale: 3–20

5. Written consent obtained from patient or the proxy

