## Methods/design

### Participants

Total 300 inpatients will be recruited through 5 neurology wards of general hospitals in Xi’an, China. Three subtypes of patients will be enrolled: I, non-acute ischemic stroke (time of stroke onset: 72 hours to 3 weeks); II, TIA with cerebral hypoperfusion; III, asymptomatic cerebral hypoperfusion. Outpatients showed abnormal results in carotid color Doppler and transcranial Doppler (temporal bone window) in routine physical examination, would be enrolled as asymptomatic candidates for further evaluation of cerebral perfusion state.

Prior to data collection, ethics approval have been achieved through the Medical Ethical Reviewing Committee of the Fourth Military Medical University Medical Center. Informed consent will be supported by a patient (or next to kin) information leaflet in Chinese. A consulted meeting will be developed by a study physician to ensure patients and their families understand the study procedure and consent to participation in the trial [20].

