### Study design

Multicenter, randomized, paralleled, double-blinded trial with concealed allocation of patients with cerebral hypoperfusion 1:1 to volume therapy using 6% HES 130/0.4 in 0.9% sodium chloride (Voluven, Fresenius Kabi, Germany) or 0.9% sodium chloride solution (normal saline, NS), is stratified by presence of stroke or not. We use digital subtraction angiography (DSA) to verify the severity of ICA or MCA stenosis [21], and evaluate cerebral hypoperfusion in unilateral intracranial artery territories by time to peak (TTP), one of parameters in CTP imaging [22].

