**Figure 1 F1:**
[figure not shown]
Flowchart outlining the trial protocol.

Participants will be randomized to one of two interventions: HES 130/0.4 and NS with two daily dosages in each intervention, i.e. 500 ml and 1000 ml, for 7 consecutive intervention days. A range of outcome measures (Table 1) will be used to ensure evaluation of relevant variables, based on the primary and secondary aims of the trial, clinical relevance and feasibility. Patients will be enrolled initially in the 500 ml groups. If more than 30% patients experience intolerable adverse events, the trial should be stopped. Following successful completion of 500 ml dose study, patients should be enrolled in the 1000 ml groups.

According to our preliminary study, 60% (15/25) of patients were found infarct responsible focuses in MCA territory by MRI brain scanning. To ensure comparable groups in terms of neurological status, group assignment will be stratified by having infarct responsible focuses or not. An individual not associated with the trial will use a computerized random number generator to randomly assign subjects to group. Allocation concealment will be ensured by using opaque, a sealed envelope containing group assignment.

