## Discussion

Because of the lack of reliable clinical data, the effect of volume therapy (HES 130/0.4) on cerebral hypoperfusion due to severe ICA/MCA stenosis or occlusion is largely unsettled. In this trial, three types of patients with cerebral hypoperfusion will be recruited: non-acute ischemic stroke, TIA and asymptomatic patients. Although volume therapy could possibly decrease blood viscosity and may increase cerebral perfusion or oxygen delivery, previous studies [13,24,28] focused on acute ischemic stroke with treatment windows from 6 hours to 48 hours resulted no improvement in outcome or survival at the endpoints. In this trial, we’d like to enroll patients with non-acute ischemic stroke (time of stroke onset: 72 hours to 3 weeks) for the following reasons: 1. variable cerebral hypoperfusion state and higher risk of hemorrhagic transformation may appear in patients with acute ischemic stroke (< 72hours); 2. from 72 hours to 3 weeks of stroke onset, patients’ emotional state and cerebral auto-regulation are relatively stable. Cerebral hypoperfusion with severe intracranial atherosclerosis is one of common causes of ischemic stroke and TIA. Unless the collateral blood supply is sufficient to prevent ischemia, multiple remote spot-like infarctions may occur within the hypoperfused brain territory. Certainly, the superiority of surgical interventions over medical therapy has been confirmed in symptomatic patients with severe ICA stenosis [8,29]. However, for the asymptomatic patients with severe or moderate ICA stenosis, the role of surgical interventions remains uncertain. For the patients with ICA or MCA occlusion, medication could be the only practical therapy. Unfortunately, few effective medical treatments have been developed for the treatment of cerebral hypoperfusion. In this trial, we will use NS as control to compare the effect of HES 130/0.4 on the improvement of cerebral hypoprefusion in MCA territory. By using CTP imaging to confirm the brain perfusion state [30], this trial will contribute to study the effectiveness, safety and tolerability of safety of HES 130/0.4 for patients with chronic cerebral hypoperfusion.

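### The randomisation stratum is clinical stroke in one section and a responsible MRI infarct in another, and inclusion criterion 4 leaves open whether the two can differ

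*Protocol article*

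**What the plan says.** All references are to the protocol article.

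- **Participants** names three subtypes. The first is "I, non-acute ischemic stroke (time of stroke onset: 72 hours to 3 weeks"; the others are "II, TIA with cerebral hypoperfusion; III, asymptomatic cerebral hypoperfusion". Neither of the last two has to be free of infarct on imaging.
- **Inclusion criteria**, item 4, opens "If cerebral infarction appears" and then sets three conditions: "Time of stroke onset: 72 hours-3 weeks"; MRI with DWI showing an ischaemic stroke attributable to the unilateral ICA or MCA stenosis; and "NIH stroke scale: 3–20".
- **Study design** says that the 1:1 randomisation "is stratified by presence of stroke or not".
- **Study procedures**, in the text below Figure 1, says that "group assignment will be stratified by having infarct responsible focuses or not". The stated purpose is to make the groups comparable in neurological status. The supporting figure is that 15 of 25 preliminary patients (60%) had a responsible infarct on MRI.
- **Study procedures** also makes MRI part of the work-up, to see whether an infarct lies in the hypoperfused region. The NIHSS, Barthel Index and modified Rankin Scale are assigned to patients with non-acute stroke, and Table 1 agrees.
- **Randomization procedures** has numbered opaque envelopes delivered to each participating centre.

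**The concern.** A stratified randomisation needs a single factor that every site determines in the same way before opening an envelope. Here one section uses a clinical diagnosis and another uses an imaging finding. Whether that matters depends on whether anyone can be enrolled who has one without the other, and the eligibility text does not settle this. Criterion 4 is triggered by an infarct, yet its conditions describe a clinical stroke of known date and measurable deficit. A TIA or asymptomatic patient with an infarct on MRI therefore has no clear route through the document.

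Such a patient is foreseeable. The Discussion says that, where collateral supply is inadequate, "multiple remote spot-like infarctions may occur within the hypoperfused brain territory". Five wards recruit, each with its own envelopes. If wards read the text differently, the same kind of patient could be refused in one, and drawn from either of two envelope sequences in others. Neither can be repaired after allocation.

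**Working it through.** **The plan's own figure.** 15/25 = 0.60, as stated; the exact (Clopper-Pearson) 95% interval is 38.7% to 78.9%. This is the share with a responsible infarct among all preliminary patients. It is not split by stroke, TIA and asymptomatic status, so it cannot give the share of non-stroke patients who have an infarct.

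**Passing each patient type through the rules.**

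| Patient | Criterion 4 read as any infarct | Criterion 4 read as subtype I only | Stratum, Study design | Stratum, Study procedures |
|---|---|---|---|---|
| Non-acute stroke with infarct | must meet the three conditions | must meet the three conditions | stroke | infarct |
| TIA or asymptomatic, no infarct | not triggered | not triggered | no stroke | no infarct |
| TIA with matching DWI lesion | excluded | eligible | no stroke | infarct (plausibly) |
| Asymptomatic with silent infarct | excluded | eligible | no stroke | unclear: is the lesion responsible? |

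*Reading 1, any infarct.* The last two rows have no qualifying stroke onset and would not be expected to score 3 to 20 on the NIHSS, so they are out. Every enrolled patient with an infarct is then a stroke patient. Criterion 4 also requires the stroke to be visible on MRI, so taking that to hold for all of subtype I, the two strata are the same. The cost is that subtypes II and III are narrower than Participants says.

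*Reading 2, subtype I only.* The last two rows enter, and Participants is respected. The two stratification rules can now disagree.

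Exclusion and stratum conflict are therefore alternatives, one under each reading.

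**How many patients.** The documents give no rate of MRI infarct among non-stroke patients, so any count is an assumption:

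number = 300 × (share without stroke) × (share of those with an MRI infarct).

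- 40% without stroke, 5% of them with an infarct: 300 × 0.40 × 0.05 = 6. The stroke stratum would hold 60% of patients and the infarct stratum 62%.
- 60% without stroke, 30% of them with an infarct: 300 × 0.60 × 0.30 = 54. The stroke stratum would hold 40% and the infarct stratum 58%.

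These counts treat every such lesion as responsible, so they lean high. The range only shows that the gap between the two rules could be trivial or substantial.

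**The case against.** The best defence is that the article is loosely worded but consistent in intent. The onset window in criterion 4 is the one that defines subtype I, and the NIHSS is scheduled only for stroke patients, so criterion 4 was probably written for subtype I. A responsible focus most naturally means the lesion that explains the clinical event; on that sense a silent lesion in an asymptomatic patient would not count, and the two stratification phrases come close to naming one factor. The full protocol, not shown, may define the strata operationally.

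Much of this stands. It makes Reading 2 the likelier intent and takes away most of the force of the silent-infarct example. It does not remove the TIA patient with a matching DWI lesion, who under Reading 2 has no stroke by one rule and plausibly an infarct by the other. And if the authors do use stroke and infarct interchangeably, Reading 1 follows, and Participants should then say that subtypes II and III must be infarct-free. The article states both factors and the eligibility rule, so this is conflicting text and not detail left to another document.

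A reader might infer more than the text supports:

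- That such patients are both excluded and mis-stratified. They cannot be; each outcome belongs to a different reading.
- That they go into the wrong stratum. The document fixes no right one, so the strata are inconsistent, not wrong.
- That the Discussion expects infarcts in subtypes II and III. Its sentence is conditional on poor collateral supply and does not mention these subtypes.
- That the treatment effect is biased. With concealed 1:1 allocation, either factor, applied consistently before allocation, gives a valid comparison.

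**Conclusion.** The concern holds in a limited form. The stratum has two non-identical definitions, and criterion 4 and Participants do not agree on whether a TIA or asymptomatic patient with an MRI infarct belongs in the trial. Depending on how criterion 4 is read, the result is either an unstated narrowing of the target population or a stratum that two wards could assign differently.

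The size cannot be derived; 6 to 54 of 300 is an illustration resting wholly on assumed shares. No bias in the TTP comparison is shown. The harm is weaker balance on the factor meant to secure comparable neurological status, uneven eligibility between wards, and a stratum that cannot be reproduced from the text. This should be corrected, but it does not threaten the validity of the randomisation.

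**What to change.** 1. Use one identical stratification factor in Study design and Study procedures. It should be determined and recorded before the envelope is opened, from the MRI already in the work-up; for example, a responsible infarct in the hypoperfused territory, yes or no, with a one-line definition of responsible.
2. Include that same factor in the primary analysis model. The ANOVA named under Statistical analysis can carry it.
3. Reconcile Participants with criterion 4 by stating whether the criterion applies to subtype I only or to any infarct, and align the description of subtypes II and III. This review does not say which eligibility rule is right. Limiting the criterion to subtype I would leave a TIA patient with a fresh lesion without the 72-hour limit, and the Discussion gives reasons for avoiding that early period, so the sponsor needs to settle the two together.

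The cost is wording, plus one term in the model. No new examination is needed. If envelopes have already been prepared under one of the two definitions, adopting that one in both sections avoids remaking them.

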### Exclusion criteria

Patients are excluded from the study if they met any of the following criteria:

1. Allergy to the components of HES

2. Clinical features including severe dehydration, overhydration and hydrocephalus

3. Chronic liver disease (ALT > 120 or AST > 120)

4. Chronic renal disease (Scr > 150 μmol/L)

5. Severe heart failure which correspond to NYHA heart failure classification class III or IV, or serious arrhythmia, myocardial infarction

6. Intracranial hemorrhage or structural brain lesions which can mimic stroke (e.g. cerebral tumor) by CT or MRI brain scanning.

7. Pregnant and lactating women

8. Patients suffered from epilepsy or mental sickness

9. Alcoholism or drug abuse

10. HES or other artificial colloidal solution was used within 3 months.

11. Patients participate in other clinical trial within 6 months

12. Contraindication to CT perfusion imaging (i.e. contrast allergy, metformin use or Creatinine >160 μmol/l)

13. Thrombus in lower limb vein

### Primary outcome measure

The alternation of TTP in CTP image defined as cerebral hypoperfusion-improvement 7 days after volume therapy will be the primary outcome measure.

### Secondary outcome measures

1. Cardiac-/cerebral-vascular events in three-months

2. Impaired kidney function after randomization

3. Impaired heart function at 3-day and 7-day after randomization

4. Blood-coagulation changes at 7-day after randomization

5. Neurological function scores (Table 1) at 7-day and 3-month after randomization

**Table 1 T1:** Outcome variables and assesment schedule

**Outcome variables**		**Baseline**	**Intervention period**		**Post**-**intervention**	**3 month follow**-**up**
			**Each day**	**5**^**th**^**day**		

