**Methods/design:**

By using computed tomography perfusion (CTP) imaging, the trial will evaluate the effectiveness, safety and tolerability of hydroxyethyl starch (HES) 130/0.4 for patients with extra-/intra-cranial artery stenosis and cerebral hypoperfusion. From 5 neurological inpatient wards, 300 patients will be randomly recruited for administered routine medications plus intravascular volume therapies using the equal volume of HES 130/0.4 or 0.9% sodium chloride solution. Cerebral hypoperfusion state after 7-day intervention is the primary outcome measure. The secondary outcome measures includes, impaired renal function, abnormal heart function, hematological changes, neurological dysfunctions and cerebrovascular events in peri-intervention period and/or 3-month follow-up. The sample size will allow the detection of a two-sided 5% significance level between groups in the endpoint with a power of 80%.

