**Discussion:**

The trial would provide important efficacy and safety data on the intravascular administration of HES 130/0.4 in patients with unilateral cerebral hypoperfusion. The effects on kidney function, heart function, coagulation, neurological function and cerebralvascular events will be assessed.

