***Secondary outcome measures***						
Symptoms (Neuro-check)		✓	✓		✓	✓
Blood pressure		✓	✓		✓	✓
ECG		✓	✓		✓	
DEC		✓			✓	
Blood/plasma viscosity		✓		✓		✓
Blood coagulation profile		✓		✓	✓	✓
CCr		✓		✓	✓	
Lipid profile		✓			✓	✓
MMSE		✓			✓	✓
**Patients With Stroke**	NIHSS	✓			✓	✓
	BI	✓			✓	✓
	mRS	✓			✓	✓

*ECG*, Electrocardiogram; *DEC*, Doppler Echocardiography; *CCr*, Creatinine clearance; *MMSE*, Mini-mental State Examination; *NIHSS*, National Institutes of health Stroke Scale, *BI*, Barthel Index; *mRS*, modified Rakin Scale.

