### Intervention

All participants will receive routine medications including antiplatelet therapy, statins therapy, risk factor modification and others if necessary. Intervention group will receive a prescribed dose of 0.6% HES 130/0.4 in 7 intervention days. Control group will be treated the same volume of NS each day in the intervention period. The initial 10–20 ml will be infused slowly, keeping the patient under close observation.

Although, the infusion dose of HES 130/0.4 up to 33 mL/kg/day is most commonly used in clinical trials and repetitive large doses of up to 70 ml/kg/day have been reported in the literatures [23-26]. Considering potential risks of overloading the circulatory system and increasing brain edema by overdose and the median cumulative HES dose (2465 ml, range 328 ml to 6229 ml) in resuscitation [27], two dose groups (500 ml/day and 1000 ml/day) have been chosen as cumulative dose of 3500 ml and 7000 ml.

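### Kidney function is a safety outcome with no end date, yet no creatinine test is scheduled at 3 months, so the scheduled tests cannot show whether impairment after HES persists or appears later

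*Protocol article*

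**What the plan says.** The Secondary outcome measures section lists five outcomes. Four carry a time: vascular events to three months, heart function at days 3 and 7, coagulation at day 7, and neurological scores at day 7 and 3 months. The kidney outcome reads only "Impaired kidney function after randomization".

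The relevant rows of Table 1, whose footnote expands CCr as "Creatinine clearance", are:

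| Row | Baseline | Day 5 | Post-intervention | 3 months |
|---|---|---|---|---|
| CCr | yes | yes | yes | no |
| Coagulation | yes | yes | yes | yes |
| Blood/plasma viscosity | yes | yes | no | yes |
| Lipids | yes | no | yes | yes |
| TTP (by CTP) | yes | no | yes | no |

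The abstract's Methods/design paragraph gives the time frame for the secondary outcomes as a group: "impaired renal function, abnormal heart function, hematological changes, neurological dysfunctions and cerebrovascular events in peri-intervention period and/or 3-month follow-up". Its Discussion paragraph puts the kidney first among the safety effects: "The effects on kidney function, heart function, coagulation, neurological function and cerebralvascular events will be assessed". The Intervention section fixes the exposure: "two dose groups (500 ml/day and 1000 ml/day) have been chosen as cumulative dose of 3500 ml and 7000 ml".

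**The concern.** Safety is a stated objective, and kidney function is the only secondary outcome without a time point. The schedule therefore decides what the outcome can mean, and it stops at the post-intervention visit. The day-5 sample falls during the 7-day infusion course, so only one scheduled CCr follows the end of treatment.

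Two questions are left open. A fall in CCr found post-intervention cannot be followed to see whether it resolves. A fall that develops afterwards is not seen in either arm. No other listed outcome fills the gap, because the three-month events are cardiac and cerebrovascular only. A creatinine change without symptoms would go unrecorded.

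Persistence matters here because some participants have only TIA or are asymptomatic, so a lasting kidney effect would weigh heavily in their balance of benefit and risk. The higher dose also exceeds the one cumulative range that the Intervention section cites (328 to 6229 ml) by 7000 − 6229 = 771 ml. The trial will have to supply much of its own kidney evidence at that exposure.

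**Working it through.** **Exposure (the plan's own figure).** 500 ml/day × 7 days = 3500 ml and 1000 ml/day × 7 days = 7000 ml. Both agree with the Intervention section.

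**Time after the last CCr.** Assumptions: infusion on days 1 to 7, and 3 months = 90 days from randomization. Table 1 does not date the post-intervention visit, and the text allows two readings.
- Day 7, since the secondary outcomes count days from randomization: 90 − 7 = 83 days; 83/90 = 92%.
- Seven days after the last infusion, a reading that the Primary outcome measure section permits, so about day 14: 90 − 14 = 76 days; 76/90 = 84%.

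**Completers.** The Sample size estimates section gives 300 patients in four groups and 20% attrition. 300 × 0.80 = 240 completers. With an equal split, this is 60 per dose and arm, or 120 per arm with the doses pooled.

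**What a 3-month test would estimate.** If no HES completer is impaired at 3 months, the one-sided 95% upper bound is 1 − 0.05^(1/n).
- n = 60 (one dose): 1 − 0.05^(1/60) = 4.9%.
- n = 120 (pooled): 1 − 0.05^(1/120) = 2.5%.

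The present schedule gives no 3-month estimate.

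**What it could test.** Power of a two-sided 5% Fisher exact test. All rates are assumed, since the article gives none.

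| Per arm | HES | Saline | Power |
|---|---|---|---|
| 120 | 12% | 2% | 84% |
| 120 | 10% | 2% | 68% |
| 120 | 10% | 5% | 22% |
| 120 | 5% | 2% | 13% |
| 60 (single dose) | 10% | 2% | 28% |

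Only a large contrast with both doses pooled reaches conventional power. Within the 7000 ml stage, where the question is sharpest, power is low even for 10% versus 2%.

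**The case against.** **The article contains no contradiction.** A reader might infer that the schedule breaks a promise made in the abstract. It does not. The abstract's wording lets any one outcome be confined to the period around the intervention, and its Discussion paragraph promises only an assessment. CCr at day 5 and post-intervention against a concurrent blinded saline arm is an assessment. The article never undertakes to measure lasting impairment. This objection stands, so the point is a gap in follow-up and not an inconsistency.

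**The full protocol or SAP may settle the window.** The definition of impairment and the exact window can be left there. The sample cannot, because no analysis plan can recover a test that was not drawn, and the article prints the whole visit schedule with this cell empty.

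**Heart measures stop at the same visit.** ECG and echocardiography also have no 3-month tick. That matches the heart outcome, which ends at day 7 by its own wording. The kidney outcome has no such end.

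**Coagulation proves little.** Its outcome is "Blood-coagulation changes at 7-day after randomization", yet "Blood coagulation profile" is also ticked at 3 months. This shows that extra data are collected there. It does not show that kidney data are owed, only that blood is available.

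**Contrast.** The second CTP is scheduled at the same visit as the last CCr, and the scan's listed contraindications ("contrast allergy, metformin use or Creatinine >160") show that contrast is used. A reader might infer that contrast confounds the kidney comparison. The documents do not support this: both arms have the same two scans, and the order of blood sample and scan is not stated. A 3-month sample would also mostly miss a transient contrast effect, so contrast is no argument for this fix.

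**A later last visit softens the point.** If the post-intervention visit falls a week after the last infusion, some recovery can already be seen there. The gap is then 84% of the 90 days and not 92%, which is still long.

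**Conclusion.** The point holds as a cheap improvement to a secondary safety outcome. Kidney function is followed from randomization with no stated end, and the scheduled tests stop 76 to 83 days before 3 months (84% to 92% of 90 days). They can compare HES with saline around the infusion. They cannot show whether a fall in CCr after 3500 or 7000 ml persists, or whether one begins later. The limit applies to scheduled tests: a clinically evident renal event could still come to light, but none is a listed 3-month outcome.

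The size rests on a 90-day count from randomization, infusion on days 1 to 7, and the two readings of the post-intervention visit. The completer numbers assume 20% attrition spread equally over four groups.

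Three stronger conclusions do not follow. The peri-intervention kidney comparison is not invalid. Nothing here shows that 7000 ml is unsafe. And a 3-month creatinine would not give a well-powered test: at an assumed 10% versus 5%, power is 22% with 120 per arm. Its value is a descriptive estimate with a bound. The primary outcome and the randomization are unaffected.

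**What to change.** Add serum creatinine, with clearance estimated from it, to the 3-month column of Table 1 for every patient, in both arms and at both dose levels. Use the same estimate at the earlier visits, so that values are comparable.

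Report two kidney results under one definition of impairment: change from baseline to day 5 and to post-intervention, and impairment at 3 months. Present the 3-month result by arm and dose as an estimate with its confidence limit, not as a powered hypothesis test.

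The cost is about 240 further serum creatinine assays (120 HES and 120 saline completers) on blood already drawn at an existing visit. Serum creatinine is specified because a measured clearance may need a timed urine collection, and the article does not say which method is used. Dose, staging, blinding, sample size and CTP schedule stay as they are. Patients already past 3 months when the change takes effect cannot be recovered, so it should be made early.
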